### Statistical methods

Bootstrap resampling technique will be used to account for repeated measures to estimate standard errors and confidence intervals. Only MRI nearest to the time of GALAD, US and/or AFP evaluation will be included in the analysis. For time-to-event data, we will use the Cox proportional hazards regression model with covariates tailored to the hypothesis under investigation. For hypotheses involving repeated measurements, events, counts, or other discrete responses, we will use either of two approaches: (1) generalized linear models with generalized estimating equations with robust variance estimation to account for the clustering, or (2) multilevel generalized linear mixed models with random coefficients to account for within-patient clustering as well as other sources of variations like clinic effects.

We will include a random intercept for each hospital site to account for variability by facility. Stratified analyses will be presented for p for interaction < 0.2. Demographic and clinical characteristics will be summarized with proportions and median (minimum–maximum) with no calculation of p-values as this is a non-randomized study. Age at liver disease diagnosis and sex will be accounted for in all analyses. Other confounders of interest include interval follow-up and insurance coverage, whereas age and gender are already controlled in the GALAD (gender, age, etc.) score calculations. All statistical analyses will be performed in SAS 9.4 (or R or another statistical software package with equivalent capabilities).

Baseline descriptions of patients with the standard of care (US and AFP) vs. GALAD score will be compared to each other. Other baseline demographics, biochemical lab results, MRI results, Fibroscan, and abdominal US in the cohort will also be described.

The interim analyses will re-evaluate the performance of the GALAD cut-off score of -0.63 after year 2 of the study. The interim analyses will not be used to assess for study events (i.e., HCC cases), and thus there will be no plan to stop the study if there were no number of events (i.e. HCC cases).

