### Study schedule and assessments

Figure 2 depicts the study schema. The study is planned for five years. Individuals with a liver mass ≥ 1 cm in diameter, elevated AFP (≥ 9 ng/mL), and/or elevated GALAD score (≥ -0.63) will be scanned with dynamic contrast-enhanced MRI, and a diagnosis of HCC will be made by LiRADS-5. Additionally, those who do not exhibit abnormal imaging findings, elevated AFP titer, and/or elevated GALAD score will obtain a dynamic contrast-enhanced MRI annually for five years to assess for HCC. In Vietnam, the study sites and the funds to be received for the study will be used for conducting all the tests and MRIs. National health insurance will not be used. In Saudi Arabia, national health insurance will cover the participants’ tests and MRIs.

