### Schedule of activities

Data will be collected during screening (initial visit) and at semi-annual intervals thereafter (a maximum of ten visits). Schedule of activities (Table 1) displays the data collection schedule for screening and follow-up.

**Table 1 Tab1:** Schedule of activities

Procedures	Screening/baseline (Visit 1)	Study Visit 2	Study Visit 3	Study Visit 4	Study Visit 5	Study Visit 6	Study Visit 7	Study Visit 8	Study Visit 9	Final Study Visit 10
Informed consent	X									
Demographics	X									
Home address/Phone number	X	X	X	X	X	X	X	X	X	X
Medical history	X	X	X	X	X	X	X	X	X	X
Collect and archive serum (15 mL blood, 50 mL urine)	X	X	X	X	X	X	X	X	X	X
Concomitant medication review	X	X	X	X	X	X	X	X	X	X
Physical exam (including height and weight)	X	X	X	X	X	X	X	X	X	X
Vital signs	X	X	X	X	X	X	X	X	X	X
Height	X									
Weight	X	X	X	X	X	X	X	X	X	X
Waist circumference	X	X	X	X	X	X	X	X	X	X
Performance status	X	X	X	X	X	X	X	X	X	X
Handgrip strength measurements	X	X	X	X	X	X	X	X	X	X
Hematology	X	X	X	X	X	X	X	X	X	X
Serum chemistry	X	X	X	X	X	X	X	X	X	X
Adverse event review and evaluation		X	X	X	X	X	X	X	X	X
Radiologic/Imaging assessment (Abdominal Ultrasound and/or cross section imaging if triggered)	X	X	X	X	X	X	X	X	X	X
Dynamic contrast-enhanced CT or MRI	X		X		X		X			X
Fibroscan	X									X
Complete Case Report Forms (CRFs) that have clinical data and events	X	X	X	X	X	X	X	X	X	X

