### Follow-up visits

Semi-annual follow-up visits will be scheduled at 22 to 26-week intervals after enrollment. Each visit has an ideal date for a visit, a lower window date (opening date for the window), and an upper window date (closing date for the window). The dates for a specific participant are specified on their visit time windows sheet. In addition to the activities in Table 1, new procedures and forms are to be completed at each of the follow-up visits (at 6, 12, 18, 24, 30, 36, 42, 48, and 54 months) are:Follow-up medical history (medication changes, key events or interventions, surgeries)Hospital admissions, new diagnoses of co-morbidities, complications of liver disease (variceal bleeding, ascites, edema, hepatic encephalopathy), liver cancer, other cancer, diabetesPhysical examinationAbdominal US and AFPLaboratory data (hematology, glucose, insulin, clinical chemistry, hepatic panel, HbA1c, lipid profile)Blood collection for plasma bankingDocumentation of any additional liver biopsies performed

Additionally, annually, each study participant will obtain a dynamic MRI with contrast to evaluate for liver cancer.

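### At five of nine follow-up visits the MRI depends on GALAD itself, and the nearest-MRI rule does not settle how all-negative unscanned visits enter the accuracy estimates

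*Protocol article*

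**What the plan says.** The places are all in the protocol article.

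- **Visits.** Follow-up visits fall "at 6, 12, 18, 24, 30, 36, 42, 48, and 54 months" (Follow-up visits), which is nine visits, numbered 2 to 10.
- **Scheduled reference scan.** In Table 1 the row "Dynamic contrast-enhanced CT or MRI" is marked at Visits 1, 3, 5, 7 and 10. The row that covers every visit reads "Radiologic/Imaging assessment (Abdominal Ultrasound and/or cross section imaging if triggered".
- **Trigger.** Study schedule and assessments: participants with a mass of at least 1 cm, "elevated AFP (≥ 9 ng/mL), and/or elevated GALAD score (≥ -0.63) will be scanned with dynamic contrast-enhanced MRI". Test-negatives "will obtain a dynamic contrast-enhanced MRI annually for five years to assess for HCC".
- **Pairing.** Statistical methods: "Only MRI nearest to the time of GALAD, US and/or AFP evaluation will be included in the analysis". The abstract and the Screening section carry the same rule. No time window or direction is given.
- **Outcome without a scan.** An item under Outcome ascertainment and study exit definitions can be read as treating the outcome as captured, with no MRI needed, when GALAD is below the cut-off and the ultrasound is normal.
- **Repeated results.** "Bootstrap resampling technique will be used to account for repeated measures to estimate standard errors and confidence intervals". The same section also names GEE and multilevel mixed models for clustering, and Cox models for time-to-event data.
- **What is compared.** Study schedule and assessments names sensitivity for early HCC (the primary measure) and false-positive results.

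**The concern.** At the five visits without a scheduled scan, a GALAD-positive result is verified at once. A GALAD-negative result is verified at that visit only if AFP or ultrasound happens to be positive. This is test-dependent verification. Its effect on the point estimates depends on what is done with the all-negative visits, and the plan does not say.

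The nearest-MRI rule does not decide it. Visits 2, 4 and 6 lie midway between two scheduled scans. With visits 22 to 26 weeks apart, a few weeks' difference in attendance decides whether the earlier or the later scan is nearest.

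Sensitivity and the false-positive rate are the quantities the study exists to estimate. The year-2 interim analysis also re-evaluates the -0.63 cut-off, which is itself one of the triggers for the scan, so any distortion would enter that review too.

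**Working it through.** **Figures in the plan.** The protocol states no GALAD sensitivity or specificity, so there is no accuracy figure to reproduce. The visit count can be checked. Scheduled scans after baseline are at Visits 3, 5, 7 and 10 (4 of 9), and there is none at Visits 2, 4, 6, 8 and 9 (5 of 9). Placing the annual scans at 12, 24, 36 and 48 months instead still leaves 5 of 9 without one.

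**Specificity if only visits with their own MRI are pooled.** Let g be GALAD's false-positive rate per visit and s that of AFP and ultrasound combined, independent of each other (both assumed). For an HCC-free participant over nine visits:

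- false positives verified = 9g
- true negatives verified = 4(1 − g) + 5(1 − g)s
- apparent specificity = true negatives / (true negatives + false positives)

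With g = 0.10 and s = 0.05: true negatives = 3.6 + 0.225 = 3.825, and 3.825 / (3.825 + 0.9) = 0.810.

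| True specificity | s = 0.05 | s = 0.10 |
|---|---|---|
| 95% | 90.0% | 90.5% |
| 90% | 81.0% | 81.8% |
| 80% | 65.4% | 66.7% |

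At a true 90%, the apparent false-positive rate rises from 10% to 18–19%.

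**Effect on the comparison of tests.** With g = 0.10 and s = 0.07, AFP and ultrasound taken together have a true specificity of 93%. Their apparent value is 0.93 × 4.5 / (0.93 × 4.5 + 9 × 0.07) = 4.185 / 4.815 = 86.9%. GALAD's is 0.90 × 4.35 / (0.90 × 4.35 + 0.9) = 3.915 / 4.815 = 81.3%. A true gap of 3 points becomes 5.6.

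**Sensitivity, and the other readings.** I simulated 1,000,000 participants over nine half-yearly visits, with exit at detection and an error-free MRI. Assumed inputs: 2% HCC per year (between the protocol's 1% and 4%); GALAD positive in 50% of tumours at the first visit and 70% later; AFP/ultrasound positive in 45% of tumours, with 7% false positives; GALAD false positives 10%; results independent between visits.

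| How all-negative interim visits enter | Sensitivity | Specificity |
|---|---|---|
| True visit-level values | 52.7% | 90.0% |
| Dropped (only visits with their own MRI) | 61.0% | 81.3% |
| Counted as HCC-free | 61.0% | 90.0% |
| Given the next MRI's result | 36.0% | 89.9% |

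Giving these visits the previous MRI's result is the same as counting them HCC-free, because anyone with HCC on that scan has left the cohort. At 1% or 4% incidence the values move by 0.2 points or less.

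**Other inputs.** Take GALAD at 70% sensitivity and 90% specificity, AFP/ultrasound sensitivity 50–70% and specificity 85–95%, incidence 1% or 4%, and results either independent or fixed within a tumour. Dropping the visits then gives specificity of 80.8–82.6% and sensitivity 3.4 to 6.7 points above the true visit-level value. Next-MRI labelling gives sensitivity of about 42–48% against 63–71%.

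**Candidate replacements, first set of inputs.** Specificity from all results in cycles that close HCC-free is 95.0%, 90.0% and 80.0% for true values of 95%, 90% and 80%. The share of cancers with a positive GALAD at the detecting visit is 61.0%. The share with any positive GALAD in the cycle is 62.5%, 64.1% and 67.0% as GALAD's false-positive rate goes from 5% to 10% to 20%. It rises because chance positives, already refuted by a negative triggered MRI, are credited when a cancer appears later in the cycle.

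**The case against.** A reader might infer that specificity will be understated and sensitivity overstated, without condition. The documents do not support that. Both directions need the rule that a visit counts only when it has its own MRI, and the protocol says nearest, not same-visit. Under the other permitted readings specificity is about right, and under next-MRI labelling the sensitivity error reverses.

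Nor does the protocol define sensitivity per visit. Everyone has recurring scheduled MRI and leaves at HCC, so a tumour missed at one visit is normally found at a later scan. The 61% is then exactly the share of detected cancers with a positive GALAD at detection, which is a legitimate quantity. It is an overstatement only against a visit-level benchmark.

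A reader might also infer that the bootstrap is the only method offered for repeated results. It is not: GEE, mixed models and Cox models are named. They address clustering or event times, not who was scanned, so this does not remove the problem.

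Finally, the labelling of interim visits might be left to an unseen analysis plan. That would carry weight if the article were silent. It fixes a pairing rule and repeats it, that rule gives no single answer midway between scans, and the outcome-ascertainment item can be read as a different rule.

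**Conclusion.** The point holds in conditional form. Verification depends on the index test at five of nine follow-up visits, and the stated rules do not fix how all-negative interim visits enter the accuracy estimates. Under the assumed inputs, the permitted readings put specificity at about 81% or 90% for a true 90%, and sensitivity at about 36% or 61% for a true visit-level 53%. No reading tried recovers visit-level sensitivity. Read per cancer, the 61% is sound, but the plan does not define it that way. None of the named methods corrects the point estimates.

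The visit count and the absence of a settled rule come from the documents. The sizes rest on assumed accuracy, independent false positives and an error-free MRI. The matter should be settled before the year-2 interim analysis.

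**What to change.** In Statistical methods, replace the nearest-MRI rule with a primary accuracy analysis by cycle between scheduled MRIs:

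1. Assign each follow-up visit to the one cycle that closes at or after it, so that no visit sits in two cycles.
2. Estimate specificity from all GALAD, AFP and ultrasound results in cycles that close HCC-free, including all-negative interim visits.
3. Define sensitivity per cancer: the share of all HCCs found, by triggered or scheduled scan, with a positive GALAD at the detecting visit. Do not count an earlier positive already followed by a negative triggered MRI. Label the result per cancer, not per visit.
4. Resample participants, not visits, in the bootstrap.
5. State how cycles left open by drop-out are handled.
6. Align the outcome-ascertainment item on visits without MRI with these rules.

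Weighting by the chance of verification at the same visit is not an alternative, since under the schedule an all-negative interim visit has no chance of a scan.

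Two inconsistencies must also be reconciled. Table 1 leaves 18 months between the scans at Visits 7 and 10, whereas Study schedule and assessments and Follow-up visits both say annually. The schedule text lists AFP as a trigger, whereas the Fig. 2 legend does not.

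The cost of the analysis change is wording only, with no new scans or data. The downside is small: sensitivity is per cancer, so a tumour that GALAD missed at one visit and flagged at a later detecting visit counts as detected.

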**Methods:**

We plan to recruit a cohort of 1,600 patients, male or female, with advanced fibrosis or cirrhosis (i.e., F3 or F4) and MELD ≤ 15, in Vietnam and Saudi Arabia (*n* = 800 each). Individuals with a liver mass ≥ 1 cm in diameter, elevated alpha-fetoprotein (AFP) (≥ 9 ng/mL), and/or elevated GALAD score (≥ -0.63) will be scanned with dynamic contrast-enhanced magnetic resonance imaging (MRI), and a diagnosis of HCC will be made by Liver Imaging Reporting and Data System (LiRADS) assessment (LiRADS-5). Additionally, those who do not exhibit abnormal imaging findings, elevated AFP titer, and/or elevated GALAD score will obtain a dynamic contrast-enhanced MRI annually for five years to assess for HCC. Only MRI nearest to the time of GALAD score measurement, ultrasound and/or AFP evaluation will be included in the diagnostic validation analysis. MRI will be replaced with an abdominal computed tomography scan when MRI results are poor due to patient conditions such as movement etc. Gadolinium-ethoxybenzyl-diethylenetriamine pentaacetic acid-enhanced MRI will not be carried out in study sites in both countries. Bootstrap resampling technique will be used to account for repeated measures to estimate standard errors and confidence intervals. Additionally, we will use the Cox proportional hazards regression model with covariates tailored to the hypothesis under investigation for time-to-HCC data as predicted by time-varying biomarker data.

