### Screening

Before or during the first visit, patients with chronic liver diseases, including advanced fibrosis/cirrhosis identified by ICD-10 from participating clinical sites, will be screened.

The screening criteria are MELD ≤ 15, non-invasive indices, and finally confirmed by Fibroscan or ARFI elastography results to further select those with fibrosis score F3 or higher from the 10 clinical centers’ databases in this Study Cohort Database (Fig. 1 & 3). All patients will be required to have a negative dynamic contrast-enhanced MRI upon study enrollment to rule out HCC before the study enrollment. Only MRI nearest to the time of GALAD score or abdominal ultrasound (US) and or AFP evaluation will be included in the analysis. If patients have a history of metal in their heads or eyes, they will need an x-ray of their skull to find out if the MRI is safe for them.

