### Outcome ascertainment and study exit definitions

Time of positive surveillance: latest date of visit with lab resultsCriteria for outcome assessment: elevated GALAD score and/or suspicion of liver tumor on ultrasound, whichever comes firstDate of detection of liver tumor ≥ 1 cm in size on dynamic contrast-enhanced MRI or confirmation of HCC on biopsyOutcome captured if multiphase MRI with contrast is not needed when GALAD score is less than the cut-off and ultrasound findings are normal.Tumor of any size and quantity will be recorded.Person-years of follow-up time: calculated for each participant from one year after the enrollment date to the event date (indication for multiphase MRI with contrast; HCC diagnosis; date of loss to follow-up, or end of study, whichever comes first).Time to event: from entry in the study to the date of liver tumor detection on multiphase MRI with contrast or on the date of biopsy with HCC confirmation.GALAD score and ultrasound: within four weeks of the visit with indicationLoss to follow-up: 12 months of last clinic encounter with no study visitsEnd of study: completion of the last visit or procedure shown in Table 1 or when a patient develops HCC and then subject to the local management protocol (above)

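### The nearest-MRI rule has no direction or maximum gap, so test-negative mid-year visits can be checked against an earlier scan that by design shows no diagnosed HCC

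*Protocol article*

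**What the plan says.** The pairing rule appears three times in the Protocol article. Statistical methods has: "Only MRI nearest to the time of GALAD, US and/or AFP evaluation will be included in the analysis". The abstract's Methods paragraph gives the same rule for scans that "will be included in the diagnostic validation analysis", and Screening repeats it. None of the three says whether the MRI may precede the blood draw, how far away it may lie, or how ties are broken.

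The schedule around the rule is as follows.

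- Follow-up visits section: "Semi-annual follow-up visits will be scheduled at 22 to 26-week intervals after enrollment", and "annually, each study participant will obtain a dynamic MRI with contrast to evaluate for liver cancer".
- Table 1, row "Dynamic contrast-enhanced CT or MRI": marked at Visits 1, 3, 5, 7 and 10, and not at Visits 2, 4, 6, 8 and 9.
- Study schedule and assessments: a liver mass of at least 1 cm, AFP of at least 9 ng/mL or GALAD of at least -0.63 leads to an MRI. No timing is given.
- Screening: "All patients will be required to have a negative dynamic contrast-enhanced MRI upon study enrollment to rule out HCC".
- Outcome ascertainment and study exit definitions: the study ends for a participant "when a patient develops HCC and then subject to the local management protocol".

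The text under Fig. 2 names sensitivity for early HCC detection as the primary outcome measure.

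**The concern.** GALAD is measured about twice as often as MRI is scheduled. A positive GALAD is verified by the MRI that it triggers. A visit at which nothing triggers has no scan of its own unless a scheduled one falls there, and it lies roughly midway between the scan before and the scan after.

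The earlier scan is uninformative about cancer at the visit. The entry MRI must be negative, and a patient diagnosed with HCC leaves follow-up, so any earlier scan of a patient still attending shows no diagnosed HCC. Pairing backwards therefore falls on test-negative visits and can only turn a potential false negative into a true negative. Which visits are affected depends on a few days' difference in attendance or booking. The estimate at stake is the primary one, and the GALAD cut-off is to be re-evaluated after year 2.

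**Working it through.** The plan states no figure for the pairing itself. Its expected case numbers reproduce: 1,600 × 0.01 × 5 = 80 and 1,600 × 0.04 × 5 = 320.

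**Step 1. Share of untriggered visits paired backwards.** Inputs are gaps of 22 to 26 weeks (Follow-up visits) and MRI at Visits 1, 3, 5, 7 and 10 (Table 1). Assumptions: gaps are uniform and independent, MRI falls on the visit date, and no other trigger fires. A visit pairs backwards when its time since the previous MRI is shorter than its time to the next.

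- Visits 2, 4 and 6: one gap on each side, so by symmetry 50%.
- Visit 8: 22–26 weeks back to Visit 7, 44–52 weeks forward to Visit 10, so 100%.
- Visit 9: 44–52 weeks back, 22–26 weeks forward, so 0%.
- Average: (50 + 50 + 50 + 100 + 0) / 5 = 50%.

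**Step 2. Sensitivity to booking.** Let D be the difference between two adjacent gaps. It is triangular on −4 to +4 weeks, so P(D < 2) = 1 − 2²/32 = 0.875 and P(D < −2) = 0.125. The baseline MRI stays at week 0.

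- Later MRIs two weeks after the visit: Visit 2 needs D < 2 (87.5%); Visits 4 and 6 need D < 4 (100%). Average (87.5 + 100 + 100 + 100 + 0) / 5 = 77.5%.
- Later MRIs two weeks before the visit: Visit 2 needs D < −2 (12.5%); Visits 4 and 6 need D < −4 (0%). Average (12.5 + 0 + 0 + 100 + 0) / 5 = 22.5%.

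The range is about 23% to 78%; at Visit 4 or 6 alone it is 0% to 100%. With strictly annual MRI at months 0 to 48, the on-date average is 60%, because the month-54 visit has no later scan.

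If ultrasound or AFP triggers a same-visit MRI showing the HCC in a fraction u of GALAD-negative visits followed by HCC, the 50% becomes 50% × (1 − u): 37.5% at u = 0.25 and 25% at u = 0.50.

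**Step 3. Effect on sensitivity.** A simulation used Table 1 MRIs on the visit date. The remaining inputs are assumptions, not in the documents: HCC onset 2% a year, specificity 90%, an MRI that finds every tumour present, triggered MRI on the visit date, and ultrasound finding 0% or 50% of tumours. The AFP trigger was not modelled separately.

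| Ultrasound finds | Assumed same-visit sensitivity | Nearest MRI | Next MRI | Gap |
|---|---|---|---|---|
| 0% | 0.50 | 0.45 | 0.34 | 0.11 |
| 0% | 0.60 | 0.53 | 0.41 | 0.12 |
| 0% | 0.70 | 0.60 | 0.47 | 0.13 |
| 0% | 0.80 | 0.67 | 0.53 | 0.14 |
| 50% | 0.50 | 0.42 | 0.33 | 0.09 |
| 50% | 0.60 | 0.50 | 0.39 | 0.11 |
| 50% | 0.70 | 0.57 | 0.46 | 0.11 |
| 50% | 0.80 | 0.65 | 0.52 | 0.13 |

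Of tumours already present at a GALAD-negative visit, about 10% (ultrasound 50%) to 21% (ultrasound 0%) are scored HCC-free under the nearest rule. Of the backward-paired negative visits later followed by HCC, only about 7% to 28% already had a tumour. With strictly annual MRI the gap between the rules is 8 to 12 points.

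**The case against.** **Inflation above the truth.** A reader might infer that the rule pushes GALAD's sensitivity above its true value. The table does not show that: without the ultrasound trigger, nearest-MRI results lie 5 to 13 points below the assumed same-visit sensitivity and next-MRI results 16 to 27 points below. Next-MRI linkage counts tumours that arise after the draw as misses, so the 9 to 14 points partly reflect a different estimand. What remains is that tumours present at the draw are scored as absent, and only among test-negatives.

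**Half misclassified.** A reader might also infer that about half of GALAD-negative mid-year visits followed by HCC are wrongly scored. Half is the share paired backwards under one set of timing assumptions. Most of those visits precede tumour onset in the simulation.

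**Unit of analysis.** The rule says which MRIs enter, not that every GALAD visit does. Read from the MRI side, or at case level, a mid-year visit without a scan may never count as a true negative and the problem largely disappears. That reading is possible, but the text does not fix it, and the bootstrap for repeated measures points towards visit-level data. The time-varying Cox model is not shown to be affected.

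**Detail for the SAP.** Direction and window are often left there, and a SAP may settle them. But the article does state a rule, three times, and as stated it permits backward pairing.

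**The test deciding its own outcome.** Outcome ascertainment has an unclear sentence treating the outcome as captured without MRI when GALAD is below the cut-off and ultrasound is normal. One might conclude that GALAD settles its own reference standard. Study schedule and Follow-up visits give test-negative patients annual MRI, so this does not follow. The sentence may mean only that no off-schedule scan is needed.

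**Conclusion.** The concern holds for a visit-level analysis: a stated rule allows test-negative visits to be verified backwards, and test-positive visits, which trigger their own MRI, are not exposed to this. GALAD results at scheduled-MRI visits are unaffected.

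The size is uncertain. The share paired backwards rests on MRI timing that the article does not give, and the effect on sensitivity rests on the assumed incidence, accuracy and ultrasound yield. That a two-week booking shift moves the share so far is itself the argument for fixing the rule. It should be settled before the year-2 re-evaluation of the cut-off. It is a correctable linkage rule, not a defect in the data to be collected.

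**What to change.** In the abstract's Methods, Screening and Statistical methods, replace the nearest-MRI rule. Link each GALAD, ultrasound and AFP result to the first MRI on or after the blood draw within a pre-stated look-ahead, for example reported at 6 and 12 months, and never to an earlier MRI. Class a visit with no MRI in the window as unverified, not HCC-free, and report the number unverified by GALAD result. State that the estimate is look-ahead sensitivity.

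Clarify the outcome-captured sentence in Outcome ascertainment so that no visit is classed HCC-free without a later negative MRI. Two further points must be reconciled: that section omits the AFP trigger given in Study schedule, and Table 1 shows no MRI at Visit 9 although Study schedule and Follow-up visits describe annual MRI.

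The cost is wording and re-linking of data already planned, with no added scans or patients. Reported sensitivity may be lower. Under Table 1, Visit 8 lies 44 to 52 weeks before the next scheduled MRI, so a 6-month window leaves every untriggered Visit 8 unverified while triggered visits stay verified. The 12-month window is therefore needed as well. Both windows should be defined in weeks with an allowance for booking, since 26 and 52 weeks sit at the edge of the visit gaps.
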